### Primary outcome measures

The primary outcome measures will be *change in ER* and *emotional wellbeing* immediately post-intervention, at 3 months post-intervention, and 6 months post-intervention. *ER* will be assessed by two constructs: the level of emotional awareness and the use of ER strategies*. Emotional wellbeing* will be indicated by several outcomes, namely positive and negative affect, self-esteem, quality of life, depressive- and anxiety symptoms.

#### Emotional awareness

The Dutch version of the Difficulties in Emotion Regulation Scale (DERS) is a 36-items self-report questionnaire developed to assess individuals’ identification, understanding and modulation of their own emotions [62, 102]. The DERS consists of six dimensions of emotion regulation namely Nonacceptance, Goals, Impulse, Strategies, Clarity, and Awareness. In this study, only the subscale ‘Awareness’ is administered, which reflects the tendency to percept, to attend and to acknowledge own emotions (e.g. “*I pay attention to how I feel”*) on a scale from 1 (‘almost never, 0–10%) to 5 (‘almost always, 91–100%). Higher scores indicate higher levels of awareness. The DERS demonstrated good psychometric properties for all subscales in adolescent population [102].

#### Emotion regulation

The Dutch version of the Fragebogen zur Erhebung der Emotionsregulation bei Kindern und Jugendlichen (FEEL-KJ) will be used to assess adolescents’ ER strategies [22]. The FEEL-KJ is a self-report questionnaire in which children and adolescents are asked to indicate how often they use adaptive, maladaptive, and external ER strategies in response to feelings of anger, sadness, and fear on a 5-point Likert-type scale ranging from 1 (“almost never to”) to 5 (“almost always”). The FEEL-KJ measures the use of 15 specific ER strategies. In current study, participants are asked to fill out items about 10 specific ER strategies namely *behavioral problem-solving, distraction, cognitive problem-solving, acceptance, reappraisal, revaluation, giving up, aggression, rumination, and social support.* Total scores indicates dispositions to use adaptive and *maladaptive* strategies to regulate negative emotions. The FEEL-KJ has demonstrated good psychometric properties [22, 38].

#### Positive and negative affect

The Dutch version of the Positive And Negative Affect Schedule for Children (PANAS-C) will be used to assess adolescents’ positive and negative affect [88]. Participants are asked to report in which degree, scaled from 1 (‘not at all’) to 5 (‘a lot’), they have experienced 30 positive (h*appy, energetic, proud)* and negative emotions (*vigilant, ashamed, unhappy)* in the past 2 weeks. Higher scores on the Positive Affect Score represent higher levels of positive affect, while lower scores on the Negative Affect Score represent lower levels of negative affect. The PANAS-C has shown good reliability and validity [148].

#### Self-esteem

The Perceived Competence Scale for Adolescents (CBSA) [139] is the Dutch version of the Self-Perception Profile for Adolescents (SPPA) [72] and will be used to assess self-esteem. The 35-items self-report questionnaire aims to measures six specific domains of self-worth, namely scholastic competence, social acceptance, athletic competence, physical appearance, behavioral conduct, close friendships, and global self-worth. In current study, only the last subscale will be used (e.g. ‘*some youngster are often disappointed in themselves, but other youngster are almost never disappointed in themselves).* Higher scores indicate a higher global self-worth. Research about validity and reliability is convincing [139].

*Quality of life* will be measured by the Dutch version of the KIDSCREEN-10, which is a short measure for assessing adolescents’ well-being and health-related quality of life (HRQoL) The KIDSCREEN-10 consist of 10 items (e.g.*, ‘Do you have felt full of energy?’)*, which are rated on a five-point scale ranging from 1 to 5 [112]. Higher scores represent a higher subjective health related quality of life. The KIDSCREEN-10 showed good psychometric properties [54].

#### Depressive symptoms

Depressive symptoms will be measured with the Dutch versions of the Child Depression Inventory (CDI) [86, 138], and the shortened version of the Center for Epidemiological Studies Depression scale (CES-D) [109]. The CDI consist of 27 items, which can be answered by choosing one out of three statements that best describes his or her feelings in the past 2 weeks. For example*, ‘I feel like crying everyday’, I often want to cry’, ‘I sometimes feel like crying’.* A score can be assigned to each statement, ranging from 0 to 2 [86]. The total score gives an indication of the severity of the self-reported depressive symptoms. The CDI has demonstrated satisfactory reliability and validity for measuring depressive symptoms [86, 138], but is also known as a less sensitive and reliable instrument to assess low to mild depressive symptoms [90]. Therefore, the 9-items version of the CES-D is also used. Adolescents are asked to indicate how much they have experienced an item in the past week, ranged from ‘never’ = 0, to ‘always’ = 3. For example*, ‘I was bothered by things that usually don’t bother me’* or *‘I felt fearful’.* The higher the total score, the more depressive symptoms are reported. The CES-D has shown acceptable reliability and validity in adolescent populations [110].

#### Anxiety symptoms

Anxiety symptoms will be measured with the Dutch version of the State–Trait Anxiety Inventory for Children (STAI-C) [7, 132]. The STAI-C initially consists of two subscales, but in current study, only the subscale on ‘state anxiety’ will be administered. The subscale consists of 20 items (e.g. *‘I feel happy now’)*, followed by three answer possibilities ranging from “hardly ever” to “often”. Higher scores indicate greater anxiety. High reliability and satisfactory validity are showed [133].

### Secondary outcome measures

Secondary outcomes include Dutch versions of instruments assessing social behavior, such as a*ttitudes about psychological stigmatization, relationships with peers and bullying,* and academic performance, such as *school achievement*, *school absence,* and *drop-out*.

#### Attitudes about psychological stigmatization

Adolescents’ attitudes about psychological stigmatization will be assessed by an adolescent-friendly version of the Stigma Scale for Receiving Psychological Help (SSRPH) [106]. Adolescents have to indicate whether they agree on five statements about stigmatization (e.g. *‘Going to the psychologist is a sign of personal weakness’* or ‘*Other people think it’s weird to visit a psychologist’)* on a scale range from 1 (‘Strongly disagree’) to 5 (‘Strongly agree’). A higher score indicate a higher degree of public stigma. Beginning evidence for the validity and reliability of the SSRPH in adolescent population is shown [106].

#### Relationship with peers and bullying

The Dutch version of the Olweus Bully/Victim Questionnaire (OBVQ) will be used to assess self-reported relationships with peers and bullying behavior [91, 105]. Adolescents are asked to report on their relationships at school (e.g. *‘How many good friends do you have in the classroom?’*) and to score items on being bullied in the present and the past (e.g. *‘How often have other students bullied you this school year?*’) [91]. Higher scores on part one represents better relationships with peers. Higher scores on part two represents more bullying experience. The scale has a good variability and reliability [128].

#### Academic performance

S*chool achievement* will be assessed by teachers, adolescents and school orientation. Teachers are asked to fill out the Academic Performance Rating Scale (APRS) [50], a rating scale for assessing perceptions from teachers about students’ academic competencies. This 19-items questionnaire assesses a range of specific achievement parameters, like work performance (e.g. *‘Estimate the percentage of math work completed, compared to classmates’*), academic success (e.g. *‘How quickly does this child learn new material?’)*, behavior control (e.g. *‘How often is the child able to pay attention without you prompting him/her?’)* and attention to assignments (e.g. *‘How frequently does the student accurately follow teacher instructions and/or class discussion during small-group (e.g., reading group) instruction*?). The APRS has shown high reliability and good validity [50]. Next to the teacher-report version of the APRS, adolescents are also asked to rate how they score on courses such as mathematics and languages compared with their classmates on a 5-point Likert scale, ranging from 0 = ‘really bad’ to 5 = ‘really good’. Finally, school orientation attests will be requested at group level at the end of the school year to assess how many students passed their first year of secondary school. At the end of the school year the total number of *absences* and the students that *drop-out* through the year will be requested.

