### Goals and hypotheses

The present study has three main goals. First, this study will test the effectiveness of a new school-based universal prevention program “Boost Camp”, targeted at strengthening ER skills in the stressful first year of high school. It is hypothesized that Boost Camp will improve or maintain emotional wellbeing. More specifically, it is hypothesized that Boost Camp will lead to an *increased* use of adaptive ER, *more* positive affect, a *higher* self-esteem, and a *better* quality of life in participants in the intervention condition compared with adolescents in the control condition. Moreover, *less* negative affect, *less* use of maladaptive ER and *less* depressive and anxiety symptoms will also be seen as markers of wellbeing.

Second, this study will test the effects of the program on secondary outcomes. It is hypothesized that Boost Camp will lead to *better* peer relations, *less* negative mental health attitudes, an *increase* in academic achievements, a *smaller* amount of school absenteeism and *less* school drop-out. Third, this study will examine the moderating role of child characteristics such as EF, baseline level of psychological problems, and gender. It is hypothesized that the program will be *less* effective for young adolescents with lower levels of EF and *more* effective for young adolescents with a higher baseline level of psychological problems. Finally, due to the difference in experiencing difficulties and psychological distress within the transition phase, the program is expected to have better effects for girls than for boys.

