## Methods

### Participants and procedure

Six secondary schools in the East of Flanders are contacted to participate in the study. Participants are adolescents in their first year of secondary school (7th grade, ages 11–13). The aim is to reach 300 students spread over 16 classes. We ensure the inclusion of students from different Socio Economic Status (SES) groups and various educational levels to compose a heterogeneous sample. In Belgium, there are two educational levels in secondary school. The first education level, grade A, is considered as a broad first grade in which students receive basic knowledge on technics, mathematics, or languages, with the intention to prepare them on a more specific educational program in the second grade. The second education level, grade B, is intended for students with specific needs. Both are included.

Schools that are interested are asked to participate with as many first-grade class groups as possible. If they give their consent to take part in the study, they are randomized by the researcher in a intervention or a control group. Finally, six rural schools with comparable background and meeting the same language criteria decided to participate in the study. All schools receive information letters for students and their parents, which contain detailed information about the study aims and procedure. Parents can either give or withhold their permission for including their child’s data in the study, and both parents and children are free to withdraw from the study at all times. The Boost Camp program is incorporated in the class curriculum, so all participants in the intervention condition receive the program. The advantage of incorporating the program in the class curriculum is that all adolescents participate and interact. To ensure that the intervention and the control schools place an equal emphasis on students’ mental health, teachers of all participating schools receive a workshop on care management and are invited to sign a school charter on the importance of emotional well-being of the schoolchildren.

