### Design

The effectiveness of Boost Camp will be tested by a clustered randomized controlled trial (cRCT) with two conditions, e.g. an intervention and a control condition (see Fig. 1). Randomization is clustered by school, which reduces the risk of contamination.

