### Feasibility indices

Fidelity and treatment integrity of the trainers will be assessed to estimate the feasibility of the program. Each trainer will be asked to indicate to what extent the program has been followed, the goals that have been reached, and how well they were able to guide and help the adolescents during the Boost Camp program. Further, trainers and adolescents will fill out an evaluation form about their experience of the Boost camp program with regard to the group atmosphere, adolescents’ motivation and program comprehensibility. Lastly, the program components will be taped and scored by independent coders in order to check feasibility. An overview of measurements and time points can be found in Table 1.

**Table 1 Tab1:** An overview of measurements and time points

Concept	Measurement (items)	Measurement in time points			
		T0	T1	T2	T3
Primary outcome measure					
ER					
Emotional awareness	DERS	x	x	x	x
ER strategies	FEEL-KJ	x		x	x
Emotional wellbeing					
Positive and negative affect	PANAS-C	x	x	x	x
Self-esteem	CBSA	x	x	x	x
Quality of Life	HRQoL	x		x	x
Depressive symptoms	CDI	x	x	x	x
	CES-D	x	x	x	x
Anxiety symptoms	STAI-C	x	x	x	x
Secondary outcome measure					
Social behavior					
Attitudes about stigmatization	SSRPH	x	x	x	x
Relationship with peers and bullying	OBVQ	x	x	x	x
Academic Performance					
School achievement	ARSP	x			x
	Self-report question	x			x
	School Orientation Attest				x
School drop-out	School data				x
School absence	School data				x
Moderators					
Initial psychological problems	CBCL	x			x
Executive functioning	BRIEF	x			x
Gender	Self-report question	x			

Note: FEEL-KJ = the Fragebogen zur Erhebung der Emotionsregulation bei Kindern und Jugendlichen [22], DERS = Difficulties in Emotion Regulation Scale [62], PANAS = Positive And Negative Affect Schedule for Children [88], CDI = Children’s Depression Inventory [85], CES-D = Center for Epidemiological Studies Depression Scale [109], STAI-C = State-Trate Anxiety Inventory for Children [7], CBSA = Competence Belief Scale for Adolescents [139], HRQoL = KIDSCREEN-10 well-being and health-related quality of life [112], CBCL = Child Behavior CheckList [141], OBVQ = Olweus Bully/Victim Questionnaire [91], SSRPH = Stigma Scale for Receiving Psychological Help [106], ARSP = Academic Performance Rating Scale [50], BRIEF = Behavior Rating Inventory for Executive Function [60] T0 = Baseline assessment, T1 = Post-test, T2 = 3 months follow-up, T3 = 6 months follow-up

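### Absence, drop-out and the group-level pass count are collected once, at T3, with no earlier value, which leaves these six-school comparisons imprecise and open to chance imbalance

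*Protocol article*

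**What the plan says.** Goals and hypotheses states directional secondary hypotheses: an increase "in academic achievements, a *smaller* amount of school absenteeism and *less* school drop-out".

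Academic performance fixes how the school records are obtained. For passing the year, "school orientation attests will be requested at group level at the end of the school year to assess how many students passed". For the other two, "At the end of the school year the total number of *absences* and the students that *drop-out* through the year will be requested". Table 1 marks the orientation attest, drop-out and absence at T3 only. The same table marks the teacher rating scale and the pupil's self-rating of achievement at T0 and T3.

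The unit of allocation is the school (Design: "Randomization is clustered by school, which reduces the risk of contamination"), and there are six of them (Participants and procedure: "six rural schools with comparable background and meeting the same language criteria decided to participate in the study"). The sample mixes educational levels: "The second education level, grade B, is intended for students with specific needs. Both are included". The camp takes place in the last week of September or the first week of October 2017.

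Data analysis describes a baseline-adjusted mixed model with random intercepts for school and for class within school, written for emotion regulation and wellbeing. Strengths and limitations acknowledges that randomising schools can leave the arms unlike.

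**The concern.** Schools plausibly differ in their usual pass, absence and drop-out levels, and grade A and grade B classes may differ too. With only six randomised units, one arm can by chance receive the schools with the higher usual level. An earlier value, or at least a breakdown by grade, is the usual way to take some of that out. None is requested here.

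For absence the gap is avoidable. The year total merges the weeks before the camp with the weeks after it, although the first part could serve as a baseline and the second as the outcome.

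The absence and drop-out hypotheses have no other measure, so they rest entirely on these records. A later analysis plan can choose the model, but it cannot recover information that was never requested. At stake is an apparent benefit or harm that is really chance imbalance between a few schools.

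**Working it through.** **The plan's own figure.** There is none to reproduce. The only sample-size calculation is for the FEEL-KJ. The figures below therefore rest on stated assumptions.

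**Share of the absence total that precedes the camp.** Assume a 1 September start and count calendar days.
- Earliest camp, longest period: 1 to 25 September is 24 days, and 1 September to 31 May is 272 days. 24/272 = 8.8%.
- Latest camp, shortest period: 1 September to 6 October is 35 days, and 1 September to 1 May is 242 days. 35/242 = 14.5%.

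If absence is spread evenly, a 10% reduction that begins at the camp appears in the year total as 10 × (1 − 0.088) = 9.1% to 10 × (1 − 0.145) = 8.6%.

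**Precision of the pass-rate comparison.** Inputs from the article: 6 schools and 300 pupils, so m = 50 per school if equal. The ICC of 0.02 is borrowed from its sample-size paragraph. Assumed: a 3:3 split of schools, pass rates of 80, 90 and 95%, and further ICCs of 0.05 and 0.10.

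SE² = p(1 − p)[1 + (m − 1)ICC]/m × (1/3 + 1/3); half-width = t(0.975, 4 df) × SE = 2.776 × SE; difference detectable with 80% power = 3.761 × SE.

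Example, p = 0.90 and ICC = 0.02: SE² = 0.09 × 1.98/50 × 2/3 = 0.002376, so SE = 0.0487, half-width 13.5 points, detectable difference 18.3 points.

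| Pass rate | Largest possible gain | Half-width at ICC 0.02 / 0.05 / 0.10 | Detectable difference at ICC 0.02 / 0.05 / 0.10 |
|---|---|---|---|
| 80% | 20 | 18.0 / 23.8 / 31.1 | 24 / 32 / 42 |
| 90% | 10 | 13.5 / 17.9 / 23.4 | 18 / 24 / 32 |
| 95% | 5 | 9.8 / 13.0 / 17.0 | 13 / 18 / 23 |

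In every row the detectable difference exceeds the largest possible gain. A 2:4 split is slightly worse (13.5 becomes 14.4 at 90% and ICC 0.02). An exact randomisation test at school level has 20 allocations for 3:3, so its smallest two-sided p is 2/20 = 0.10. For 2:4 it is 1/15 = 0.067.

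**Would last year's pass rate rescue it?** With 50 pupils, the binomial variance of an observed school rate is p(1 − p)/50: 32, 18 and 9.5 squared points at 80, 90 and 95% (SD 5.7, 4.2, 3.1). Even if true school levels never changed, the year-to-year correlation could be at most r = SD²/(SD² + binomial variance). A change score multiplies the interval by √[2(1 − r)], so it helps only when r exceeds 0.5.

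| Assumed school SD (points) | Highest r at 80 / 90 / 95% | Width multiplier at 80 / 90 / 95% |
|---|---|---|
| 3 | 0.22 / 0.33 / 0.49 | 1.25 / 1.15 / 1.01 |
| 4 | 0.33 / 0.47 / 0.63 | 1.15 / 1.03 / 0.86 |
| 6 | 0.53 / 0.67 / 0.79 | 0.97 / 0.82 / 0.65 |

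The change score widens the interval in five of nine cases, by up to 25%. Using a school-level baseline as a covariate (3 df) multiplies the half-width by 0.99, 0.82 or 0.50 at r = 0.5, 0.7 or 0.9, so it too needs a strong correlation.

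**The case against.** Schools are randomised, so a missing baseline is not a source of bias. The binding limit is six clusters, which affects every outcome and which no baseline removes. The article already discloses the risk of unlike arms. Passing or dropping out of the first year has no individual pre-value. Weeks before the camp occur in both arms, so they dilute a difference without tilting it. All of this stands.

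The wording about group level also needs care. It is attached to the attests only, and it may mean class, since the article elsewhere speaks of class groups. Absence and drop-out may be available per pupil. A reader might infer that the pass count cannot be split by grade, that it includes pupils whose parents withheld permission, or that all three outcomes reduce to three school figures against three. The article does not say so.

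A reader might likewise infer that the whole achievement hypothesis is unanswerable. It is not: two of its three measures have T0 and T3 values.

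Finally, it can be argued that the analysis of school records belongs in the full protocol or analysis plan. That is true of the model, but not of what is collected, because the article fixes the timing of all three measures, the group level of the attests and the year-total form of absence.

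**Conclusion.** The point holds as a limit on precision and on protection against chance imbalance, for three secondary outcomes. It does not support the stronger reading that a programme effect is inseparable from school differences, or that the comparison is biased.

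For pass rate, under the assumed 3:3 split, 50 pupils per school and an ICC of at least 0.02, the detectable difference exceeds the largest possible gain at all three assumed pass rates. Such data can describe but hardly test. For absence, about 9-15% of the counted period precedes the camp, given a 1 September start. That dilution is modest; the larger loss is the unused baseline. The value of that baseline depends on how strongly absence before the camp predicts absence after it, which the article does not give. Drop-out was not quantified, because no rate is given, but it has the same structure.

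**What to change.** Extend the year-end records request to the six schools:

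- **Absence:** ask for totals split at the camp date, using the same calendar date in control schools, by coded pupil where permitted and otherwise by class. Analyse post-camp absence adjusted for pre-camp absence, with random intercepts for school and for class within school.
- **Pass and drop-out:** ask for counts by class and grade A/B, with denominators. Report both as descriptive comparisons that respect clustering by school, not as tests of the second-goal hypotheses.
- **Prior-year school rates:** these may be requested as context or as a covariate. A change from the prior year should not be the planned analysis, because with about 50 pupils per school it can widen the interval.
- **Text:** state that teacher-rated and self-rated achievement, which have T0 values, carry the achievement hypothesis.

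The cost is minor administrative work for six schools and a short text change, with no extra pupil contact. Precision stays low whatever is requested, because there are only six schools.
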